#### Exclusion criteria

Participants must meet none of the following exclusion criteria:

Invasively mechanically ventilated for >96 hours prior to randomisation.Expected to be disconnected from mechanical ventilation ≤24 hours after enrolment.Intubated for ≥24 hours during a prior episode of invasive mechanical ventilation during the current hospitalisation.Body mass index (BMI) ≥40 kg/m^2^.No contraction of abdominal wall muscles in response to abdominal functional electrical stimulation (determined by ultrasound).Pre-existing neuromuscular or muscular disorder that could affect the respiratory muscles (eg, spinal cord injury or Guillain-Barré syndrome).Open abdominal surgery <4 weeks prior to enrolment.Open or damaged skin at the area of electrode placements.Pacemaker and/or implanted electronic device.Known or expected pregnancy.Pharmacological paralysis at the time of enrolment (those receiving neuromuscular blockers may be enrolled after a ≥12-hour washout period).Tracheostomy prior to enrolment.On home non-invasive ventilation (except for Continuous Positive Airway Pressure (CPAP) or Bilevel Positive Airway Pressure(BiPAP) for obstructive sleep apnoea).Receiving or expected to receive comfort measures (palliative, hospice, comfort care, etc.) at the time of screening or enrolment.Participation in any of the following:A study with the same or similar primary outcome.A study investigating electrical stimulation or respiratory muscle therapy.Any study which the site principal investigator (PI) determines may interfere with the results of this study.Unable or unwilling to comply with protocol requirements, including assessments, tests and follow-up visits.Any other medical condition which, in the opinion of the investigator, will make participation medically unsafe or will interfere with the study results.Inability to obtain written informed consent from the participant or their legally authorised representative.

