### Sample size

Assuming an outcome expected subdistribution hazard ratio (active/sham) of 1.7, 1:1 group allocation, a type I error rate of 5% (two-sided), and 90% power, the targeted total number of participants successfully liberated from mechanical ventilation is 150. Based on the results of pilot studies, it is estimated that at least 55% of participants will achieve successful liberation. Thus, approximately 272 participants will be needed for the trial. The trial will continue to randomise participants until 150 events from the combined study groups have occurred, regardless of the total number of participants randomised. The final analysis will be performed after all randomised participants have completed or discontinued their participation in the study.

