#### Primary outcome

Cumulative incidence competing risk (CICR) estimates will be used to describe rates of successful liberation over time in the presence of a competing event. CICR curves from different treatment groups will be compared by Gray’s test at a two-sided significance level of 0.05.^37^

In the rare event that successful liberation occurs before the first VentFree treatment and any competing events, the participant will be considered as having experienced the event of interest on day 1. If any competing event occurs before both the first VentFree treatment and the event of interest, the participant will be considered as having experienced the competing event on day 1. If a participant drops out of the trial before receiving the first VentFree treatment for any reason other than successful liberation or competing events, the participant will be treated as censored on day 1.

As a supplement to the primary analysis, the cause-specific hazard ratio (*csHR*) and subdistribution hazard ratio (*subHR*) for successful liberation, accompanied by their corresponding CIs, will be computed using Cox proportional hazard model and Fine-Gray subdistribution hazard model, respectively. Robust (sandwich) variance estimators clustered by site will be used in these regression-based models to account for potential within-site correlation in this multicentre trial.

The primary analysis of the primary outcome will be based on the intent-to-treat (ITT) population, which will include all randomised participants, regardless of whether or not abdominal FES is received. Sensitivity analyses will be performed using the modified ITT population, which will include participants who receive at least one VentFree intervention session, and the per protocol population, which will include participants who receive treatment and have no major protocol deviations. In the case of any discrepancies in the conclusions derived from analyses based on different analysis populations, additional analyses will be performed to elucidate these significant differences. No interim analysis is planned.

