#### Key secondary outcomes

The key secondary outcomes—CPF and MEP measured when the participant meets the awakening/comprehension criteria but no sooner than 24 hours after the patient has been extubated—outcome will be sequentially compared between treatment groups using the ITT population in a superiority manner, provided that the active group demonstrates superiority over the sham group in the primary outcome. Each comparison will be conducted at a one-sided significance level of 0.05 using an unpaired t-test. The Wilcoxon rank-sum test will be performed as a supportive analysis to account for any potential violations of the normality assumption.

To control the family-wise type I error, the testing procedure will be carried out in a fixed sequence, starting with the primary outcome, followed by CPF and MEP. The testing will stop at the first rejection failure. This fixed sequence testing procedure guarantees that the family-wise error rate is appropriately controlled across both the primary and key secondary outcomes. Missing data for the key secondary endpoints will be imputed. For participants who have experienced competing events, the worst observed value for that parameter during the study will be imputed. For other participants, under the assumption of missing at random, a linear regression model (multiple imputation) will be used to impute the missing values for CPF and MEP. Predictors in the imputation model will include the following baseline factors: region, race, ethnicity, age, gender, BMI, COPD (yes/no), sepsis (yes/no), clinical frailty scale, steroid use (yes/no) and the Sequential Organ Failure Assessment (SOFA) score. Predictors may be removed if convergence issues arise.

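### No baseline covariates are named for the supplementary Cox and Fine-Gray models of the primary outcome; a prespecified adjusted fit beside the unadjusted one is a cheap gain

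*Protocol article*

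**What the plan says.** All references are to the protocol article.

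- **Primary test** (Statistical methods, Primary outcome): "CICR curves from different treatment groups will be compared by Gray’s test at a two-sided significance level of 0.05". No strata or covariates are named.
- **Effect estimates** (same section): the ratios are introduced with "As a supplement to the primary analysis, the cause-specific hazard ratio". This ratio and the subdistribution hazard ratio "will be computed using Cox proportional hazard model and Fine-Gray subdistribution hazard model, respectively". On variance, "Robust (sandwich) variance estimators clustered by site will be used in these regression-based models". No covariate is listed, and nothing says that treatment is the only term.
- **Baseline data** (Key secondary outcomes): the imputation model for cough peak flow and maximum expiratory pressure uses the "following baseline factors: region, race, ethnicity, age, gender, BMI, COPD (yes/no), sepsis (yes/no), clinical frailty scale", plus steroid use and SOFA.
- **Prior ventilation** (Eligibility criteria): at least 24 hours of ventilation is required, and one exclusion is "Invasively mechanically ventilated for >96 hours prior to randomisation". Each participant's prior ventilation time must therefore be known.
- **Randomisation** (Sequence generation): 1:1, stratified by country only.
- **Planning values** (Sample size): "Assuming an outcome expected subdistribution hazard ratio (active/sham) of 1.7, 1:1 group allocation", with "a type I error rate of 5% (two-sided), and 90% power", giving 150 liberations and about 272 participants.

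**The concern.** The two hazard ratios are the only between-group ratios described for the primary outcome, so they are what readers will quote. The article names model terms where it plans them: interaction terms for site and region, and eleven predictors for imputation. It names none for these two models.

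How ill a patient is, and how long he or she has been ventilated at entry (24 to 96 hours), may plausibly affect how soon liberation comes. A hazard model that omits prognostic covariates gives a ratio closer to 1 than the covariate-conditional ratio and a less efficient test. It also leaves any chance imbalance in the estimate. If SOFA or prior ventilation time turned out uneven, an adjusted ratio chosen after unblinding would carry little weight. Clustering the variance by site does not help, because it changes the standard error and not the estimate.

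**Working it through.** **1. The plan's own figures.** Inputs from Sample size: subdistribution hazard ratio (subHR) 1.7, two-sided 5%, power 90%, 1:1 allocation, 55% liberated.

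- Events (Schoenfeld): 4(1.960 + 1.282)² / (ln 1.7)² = 4 × 10.51 / 0.2816 = 149.3, rounded up to 150. This matches.
- Power at 150 events: Φ(0.5306 × √150 / 2 − 1.960) = Φ(1.289) = 90.1%.
- Participants: 150 / 0.55 = 272.7, in line with about 272.

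The planned 90% is reached with no covariate adjustment. Adjusting the supplementary models does not alter Gray's test.

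**2. Chance imbalance.** Take 272 / 2 = 136 per arm and stratification by country only.

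- The SD of a standardised mean difference is √(2/136) = 0.121.
- P(|difference| > 0.2 SD) = P(|Z| > 0.2 / 0.121) ≈ 10% for one covariate.
- For six covariates, assumed independent: 1 − 0.901⁶ ≈ 47% that at least one exceeds 0.2 SD.
- At an assumed log-subHR of 0.5 per SD, a 0.2 SD imbalance multiplies the ratio by exp(0.5 × 0.2) = 1.105. A ratio of 1.7 becomes 1.7 / 1.105 = 1.54 or 1.7 × 1.105 = 1.88.

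**3. Efficiency of the model-based test.** The article gives no prognostic strength, so it is an assumed range. All runs use 272 participants, about 147 to 150 liberations and a two-sided 5% Wald test for treatment. They use model-based standard errors, not the planned site-clustered ones.

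*(a) 1.7 read as the unadjusted (marginal) subHR, one prognostic score, 900 trials per row:*

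| SD of prognostic score (C-index) | Power, treatment only | Power, adjusted | Gain (points) | Adjusted subHR |
|---|---|---|---|---|
| 0.4 (0.60) | 90.7% | 92.8% | 2.1 | 1.77 |
| 0.6 (0.65) | 88.8% | 94.3% | 5.5 | 1.80 |
| 0.8 (0.70) | 89.4% | 96.0% | 6.6 | 1.89 |

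With six coefficients estimated instead of one score, the gains were about 3, 4 and 8 points, with a loss of about 1 point when the covariates had no prognostic value. A further six-coefficient run (1,500 trials per setting, treatment-only subHR 1.68 to 1.71) gave 2.3, 5.5 and 8.3 points, and no change when they had none. The spread between runs is of the size of simulation error.

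*(b) 1.7 read as the covariate-conditional subHR, one score, 2,500 trials per row:*

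| log-subHR per SD | Power, treatment only | Power, adjusted | Treatment-only subHR |
|---|---|---|---|
| 0 | 88.8% | 88.5% | 1.70 |
| 0.3 | 87.8% | 89.8% | 1.67 |
| 0.5 | 82.2% | 88.0% | 1.62 |
| 0.8 | 74.7% | 89.1% | 1.55 |
| 1.0 | 68.2% | 90.2% | 1.50 |

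The gaps in (b) are wider because the unadjusted ratio itself falls below 1.7. The article does not say which ratio 1.7 is. Reading (a) fits better, because the sample size formula and Gray's test both concern the unadjusted comparison of two arms. The size quoted in the verdict therefore rests on (a).

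**4. Type I error.** With no treatment effect and a log-subHR of 0.5 or 1.0 per SD, the rejection rates were 4.4% and 4.3% for treatment only, and 4.6% and 4.7% adjusted.

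**The case against.** The strongest reply is that nothing here is wrong. A covariate list for a supplementary model is ordinary SAP content, the SAP is not shown, and an unadjusted test with unadjusted ratios is valid and consistent. That stands, and it limits the point to a suggestion that lapses if the SAP already names covariates.

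Several stronger readings are tempting, but the article does not support them:

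- **The models contain treatment alone.** This would be inferred from silence; the article neither lists nor excludes covariates.
- **The primary analysis loses power.** The 5% error rate is spent on Gray's test. Every gain above belongs to a model test that decides nothing.
- **A rise from 1.7 to 1.8 or 1.9 is effect that the plan throws away.** Hazard ratios are non-collapsible. The larger value is a conditional ratio that answers a different question, and the unadjusted ratio is the one that matches the curves Gray's test compares.
- **The covariates are strong predictors.** No strength is given for any of them; only plausibly prognostic is fair.
- **Imbalance biases the result.** Over repeated randomisation it adds imprecision, and type I error is not inflated.
- **The plan makes no other use of baseline data or prior ventilation.** Exploratory Fine-Gray subgroup models use selected baseline characteristics, and a supportive analysis starts the clock at the start of ventilation. Neither gives an adjusted treatment ratio for the primary outcome.
- **The two ratios are the only summaries.** Cumulative incidence is estimated by group, and incidence of liberation is a secondary outcome.

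It is also fair to say that the simulations omit the site-clustered variance, so their figures are approximate.

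**Conclusion.** The point holds as an inexpensive improvement, not as the correction of a fault. The article names no prespecified covariates for the two models that supply the quoted ratios, so those ratios are open to chance imbalance that only a list fixed in advance can answer credibly. Under the assumptions shown, a 0.2 SD imbalance in one covariate could move a ratio of 1.7 to about 1.54 or 1.88.

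The efficiency gain for the model-based test runs from nil to about 8 points. It assumes a C-index up to 0.70, 1.7 as the unadjusted ratio, about 150 liberations and no site clustering. The trial is not shown to be underpowered, and its decision rule is unaffected.

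**What to change.** First check the SAP; if it already names covariates for these models, nothing is needed. Otherwise add the following before unblinding:

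- One Fine-Gray and one cause-specific Cox fit with treatment plus hours ventilated before randomisation, age, baseline SOFA, clinical frailty scale, COPD and sepsis.
- Both reported beside the unadjusted ratios and labelled as conditional on the covariates.
- A simple rule for missing baseline values.
- Gray's test kept, unchanged, as the primary test.

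The article keeps the blind until database lock and expects analysis to begin in April 2026, so the list has to be dated before then.

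The cost is a short SAP addition and two extra fits. Seven coefficients against 150 events is 150 / 7 ≈ 21 events each, which is comfortable. The downsides are a second, conditional estimate to explain and a negligible loss of efficiency (about 1 point at most in the runs above) if the covariates turn out not to be prognostic.

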#### Key secondary outcomes

The key secondary outcomes—CPF and MEP measured when the participant meets the awakening/comprehension criteria but no sooner than 24 hours after the patient has been extubated—outcome will be sequentially compared between treatment groups using the ITT population in a superiority manner, provided that the active group demonstrates superiority over the sham group in the primary outcome. Each comparison will be conducted at a one-sided significance level of 0.05 using an unpaired t-test. The Wilcoxon rank-sum test will be performed as a supportive analysis to account for any potential violations of the normality assumption.

To control the family-wise type I error, the testing procedure will be carried out in a fixed sequence, starting with the primary outcome, followed by CPF and MEP. The testing will stop at the first rejection failure. This fixed sequence testing procedure guarantees that the family-wise error rate is appropriately controlled across both the primary and key secondary outcomes. Missing data for the key secondary endpoints will be imputed. For participants who have experienced competing events, the worst observed value for that parameter during the study will be imputed. For other participants, under the assumption of missing at random, a linear regression model (multiple imputation) will be used to impute the missing values for CPF and MEP. Predictors in the imputation model will include the following baseline factors: region, race, ethnicity, age, gender, BMI, COPD (yes/no), sepsis (yes/no), clinical frailty scale, steroid use (yes/no) and the Sequential Organ Failure Assessment (SOFA) score. Predictors may be removed if convergence issues arise.

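### CPF and MEP are tested by an unadjusted t-test although the plan already names baseline predictors of both: a cheap, probably modest gain in precision is left unused

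*Protocol article*

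**What the plan says.** All of this is in the protocol article, Statistical methods, Key secondary outcomes, unless noted.

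- **Population and order.** CPF and MEP are "sequentially compared between treatment groups using the ITT population in a superiority manner", only if the primary outcome shows superiority, with CPF first. Testing stops at the first failure.
- **Lead test.** "Each comparison will be conducted at a one-sided significance level of 0.05 using an unpaired t-test".
- **Support.** "The Wilcoxon rank-sum test will be performed as a supportive analysis to account for any potential violations of the normality assumption". This test is also unadjusted, and the article describes no adjusted analysis of CPF or MEP.
- **Imputation after a competing event.** "For participants who have experienced competing events, the worst observed value for that parameter during the study will be imputed".
- **Imputation for everyone else.** The plan assumes that values are missing at random and fills them in by multiple imputation from a linear regression.
- **Covariates in that regression.** The article gives them as follows: "Predictors in the imputation model will include the following baseline factors: region, race, ethnicity, age, gender, BMI, COPD (yes/no), sepsis (yes/no), clinical frailty scale". The list ends with SOFA and use of steroids. Predictors may be dropped if the model does not converge.
- **Timing (Secondary outcomes).** Both outcomes are measured no sooner than 24 hours after extubation. No baseline measurement is described.
- **Stratification (Sequence generation).** Randomisation is stratified by country, which does not enter the t-test.

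**The concern.** With no baseline CPF or MEP to adjust for, baseline patient characteristics are the main means of reducing the error variance of these outcomes. The plan identifies such characteristics and builds a regression for CPF and MEP on them, but only to fill in missing values. The confirmatory comparison then leaves whatever variance they explain in the error term.

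CPF and MEP are the only confirmatory outcomes besides the primary, and they bear directly on the proposed mechanism, expiratory muscle strength and cough. Because the sequence stops at the first failure, noise that loses CPF also closes the test of MEP. The primary outcome, its Gray's test and the sample size are not affected.

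**Working it through.** **1. The plan's own figures (Sample size).** Inputs: subdistribution hazard ratio 1.7, two-sided 5%, 90% power, 1:1 allocation, at least 55% liberated. Schoenfeld's formula gives 4 × (1.960 + 1.282)² / (ln 1.7)² = 4 × 10.507 / 0.2816 = 149.3, so 150 events. Then 150 / 0.55 = 272.7, against about 272 stated. Both reproduce. About 136 per arm therefore enter the intention-to-treat comparison of CPF and MEP. The article gives no SD, effect size, R-squared or power for these outcomes.

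**2. Gain before any dilution (R-squared and base power assumed).** Adjustment multiplies the standard error (SE) by √(1 − R²). Take an effect that the t-test detects with 80% power at one-sided 0.05: (1.645 + 0.842) × √(2/136) = 0.30 SD. Adjusted power is Φ(2.486 / √(1 − R²) − 1.645). The last column is 272 / (1 − R²), the number the t-test would need for the same precision.

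| Assumed R² | SE multiplier | Power | Equivalent N |
|---|---|---|---|
| 0 | 1.000 | 80.0% | 272 |
| 0.05 | 0.975 | 81.8% | 286 |
| 0.10 | 0.949 | 83.5% | 302 |
| 0.20 | 0.894 | 87.2% | 340 |
| 0.30 | 0.837 | 90.8% | 389 |

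**3. Dilution by worst-value imputation.** Everyone with a competing event receives one constant, and that weakens the link between covariates and outcome. A simulation compared the t-test with a linear model on arm plus six covariates: 136 per arm, 2,000 runs per setting, model-based standard errors. The share given the worst value was 20%, 30% or 45%; the top value is 100% − 55%, as if everyone not liberated had a competing event. R² is among participants not given the worst value. The effect was set at twice 0.30 SD, so base power differs by row. In the last column, the covariate score has correlation 0.3 with the liability to a competing event.

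| Worst-value share | R² | Covariates unrelated to competing events: t-test → adjusted (SE ratio) | Covariates related: t-test → adjusted (SE ratio) |
|---|---|---|---|
| 20% | 0.10 | 86.6 → 86.3% (0.996) | 85.2 → 87.5% (0.954) |
| 20% | 0.30 | 86.5 → 88.4% (0.964) | 87.1 → 91.8% (0.900) |
| 30% | 0.10 | 71.2 → 71.8% (1.001) | 72.8 → 76.0% (0.956) |
| 30% | 0.30 | 71.4 → 73.4% (0.979) | 71.4 → 78.4% (0.914) |
| 45% | 0.10 | 55.0 → 54.9% (1.005) | 54.6 → 56.8% (0.960) |
| 45% | 0.30 | 53.5 → 54.1% (0.992) | 55.5 → 61.0% (0.930) |

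The gain is −0.3 to 2.0 points in the first case and 2.2 to 7.0 in the second. Put on a common 80% base through the formula in step 2, SE ratios of 1.005 to 0.964 give 79.7% to 82.5%, and 0.960 to 0.900 give 82.8% to 86.8%. The ranges are essentially the same.

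**4. Cost if the covariates are useless.** With R² of 0 and no link to competing events, the SE ratio was 1.011 to 1.012, a loss of about 1%. Simulated type I error under no effect stayed near 5% for both analyses (0.041 to 0.063 for the t-test, 0.041 to 0.060 for the adjusted model).

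**The case against.** The strongest reply is that nothing here is wrong. Under randomisation the unadjusted t-test keeps its type I error, and its standard error already allows for chance imbalance, so imbalance in age or gender is not bias. That stands. A reader might infer that the confirmatory tests are invalid or biased; the document does not support that.

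A second reply is that the gain may be overstated. A reader might assume a correlation of 0.5 (R² 0.25) and claim that power rises from 80% to 89%. The article gives no basis for that figure, and it describes no baseline CPF or MEP to which a baseline-outcome correlation could apply. In a separate large simulation (assumed CPF mean 60, SD 25, worst value 10, 30% competing events), an R² of 0.25 among tested participants fell to 0.077 overall when covariates did not predict competing events, giving 82.7% power. It stayed near 0.25 only when they predicted them at log-odds 0.8 per SD. That is the favourable corner, not the expected case.

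Third, listing variables for imputation does not assert that they are strongly prognostic: they may be there to make missing at random plausible, and the plan allows some to be dropped. This is fair. It limits what can be said about size, not the case for adjusting. Nor does the article say that CPF and MEP could not be measured at baseline; it only describes no such measurement.

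Fourth, an analysis plan that is not shown may contain adjusted supportive analyses. Their absence from the article is therefore not criticised here. The choice of lead test is stated in the article and is open to comment.

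Last, timing. Under Trial status, recruitment ended in January 2026 and analysis was expected to begin in April 2026. Replacing a stated confirmatory test that late needs a documented reason and evidence that blinding held. This stands, and it sets the condition on the fix.

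**Conclusion.** The point holds as a loss of efficiency on the two key secondary tests. The t-test is valid, but it sets aside baseline information that the plan already intends to use for the same outcomes. The likely gain from adjustment is modest: roughly 0 to 2 points of power if the covariates do not predict competing events, and about 2 to 7 points if they do. It is plausible, but not stated, that age, frailty and SOFA relate to death, palliative care or transfer for worsening condition. All these sizes rest on assumed R², base power, competing-event share and strength of association. The simulation also did not include the multiple imputation of other missing values. The case for the change is that the possible loss is about 1% in the standard error while the possible gain is several times larger. It is a cheap improvement.

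**What to change.** Make the lead analysis a linear model of CPF, and then of MEP, on treatment arm, country and a short prespecified subset of the listed covariates (for example age, gender, BMI, COPD, clinical frailty scale and SOFA). Fit it in each imputed data set and combine by Rubin's rules. Use heteroscedasticity-robust standard errors, because of the mass of participants at the worst value. Keep the unpaired t-test and the Wilcoxon rank-sum test as supportive. The fixed sequence and the significance level can stay as they are for this purpose.

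Fix the covariate list and document the change, with its reason, before database lock and unblinding. If that point has passed, keep the t-test as the lead and report the adjusted model as a sensitivity analysis.

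The cost is analysis-plan wording and a few lines of code, with no new data, visits or participants. The downsides are a standard error about 1% larger if the covariates predict nothing, an estimate that must be described as adjusted, and a late documented departure from a stated test.

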### Outcomes

#### Primary outcome

The primary outcome is time (in days) from first administration of the VentFree intervention to successful liberation from mechanical ventilation, defined as disconnection from mechanical ventilation that does not require invasive mechanical ventilation in the subsequent 7 days after disconnection,^33^ or until ICU discharge (as defined above), or until live hospital discharge, whichever occurs first.

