### Statistical methods

#### Competing events

Participants who die, are put on palliative care or are transferred out of the ICU for any reason due to a worsening condition before achieving successful liberation by day 28 or ICU discharge (whichever occurs first) will be considered to have experienced a competing event. The time from FES treatment administration to death, initiation of palliative care or ICU transfer due to worsening condition will be used for analysis. Participants who reach day 28, are discharged from the ICU or withdraw from the study before experiencing successful liberation from mechanical ventilation or a competing event will be considered right-censored at the earliest of day 28, ICU discharge or study withdrawal.

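### The worst-value rule for CPF and MEP stops at successful liberation, so a participant who is liberated and then dies or enters palliative care untested is imputed as missing at random

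*Protocol article*

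**What the plan says.** Under Key secondary outcomes, the protocol article splits participants with missing CPF or MEP into two groups. The first is defined by the primary endpoint's competing-event status: "For participants who have experienced competing events, the worst observed value for that parameter during the study will be imputed". The second is everyone else: "For other participants, under the assumption of missing at random, a linear regression model (multiple imputation) will be used to impute the missing values". The model for the second group starts from baseline information: "Predictors in the imputation model will include the following baseline factors", followed by a list that includes age, frailty, sepsis, COPD, steroid use and SOFA. It has no term for later death or palliative care.

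Under Competing events, the first group is limited in kind and in time: "Participants who die, are put on palliative care or are transferred out of the ICU for any reason due to a worsening condition", and this must happen "before achieving successful liberation by day 28 or ICU discharge (whichever occurs first) will be considered to have experienced a competing event".

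Under Primary outcome, successful liberation is "disconnection from mechanical ventilation that does not require invasive mechanical ventilation in the subsequent 7 days after disconnection", with the window ending early at other points: "or until ICU discharge (as defined above), or until live hospital discharge, whichever occurs first". Under Interventions, a transfer order to a floor team is enough to count as ICU discharge.

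The two outcomes themselves are "measured when the participant meets the awakening/comprehension criteria but no sooner than 24 hours after the patient has been extubated". They are compared in the ITT population by one-sided 5% t-tests, after a positive primary result.

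**The concern.** A worst-value rule exists so that a participant who could not be tested because of death is not credited with the strength of someone who could. Here the rule stops applying at successful liberation, while CPF and MEP may still be unmeasured. Two untested participants who die on the same day can then be given very different values, depending only on whether liberation came first.

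Liberation is what the device is meant to bring forward, and CPF and MEP are tested only when the primary result favours active. If earlier liberation moved deaths from the worst-value group to the missing-at-random group, active could appear to gain cough strength with no change in cough or survival. The article says that the fixed sequence guarantees family-wise error control. That holds only if each test in the sequence keeps its own level.

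**Working it through.** **1. The plan's own figures.** No figure is stated for CPF or MEP. The primary sample size reproduces: events = 4 × (1.960 + 1.282)² / (ln 1.7)² = 149.3, so 150, and 150 / 0.55 = 272.7 against about 272 stated. Half of 272 gives 136 per arm, used below.

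**2. Paths traced through the definitions, all untested for CPF and MEP.**

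| Path | Status | Imputation |
|---|---|---|
| Ventilated until death on day 20 | Competing event | Worst value |
| Disconnected day 8, reintubated within 7 days, dies in the ICU by day 28 | Competing event | Worst value |
| Disconnected day 8, not reintubated, dies in the ICU within 7 days | Not settled by the text | Either |
| Disconnected day 8, not reintubated, never meets awakening criteria, dies in the ICU on day 20 | Liberated | Missing at random |
| Disconnected, transfer order to the floor, then dies on the ward | Liberated | Missing at random |

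The last two rows are the defect. They are liberated on any reading of the primary definition.

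**3. Size, on assumptions.** The documents give no rate of untested death, no split around liberation and no CPF or MEP distribution. I assume:
- values with SD 1 and no treatment effect;
- the same proportion m dying untested in each arm, all other participants tested;
- shares s_S (sham) and s_A (active) of those deaths falling after liberation;
- a worst observed value of −2.65 SD (expected minimum of 150 normal values), and missing-at-random draws averaging 0 (no covariates).

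With p = m × (1 − s) at the worst value in each arm:
- spurious difference d = m × (s_A − s_S) × 2.65
- variance in an arm = (1 − p) + p(1 − p) × 2.65²
- SE = √[(sum of the two variances) / 136]
- rejection rate = 1 − Φ(1.645 − d/SE)

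Example: m = 25%, s_S = 10%, s_A = 14%. Then p = 0.225 and 0.215, the variances are 2.00 and 1.97, SE = √(3.97/136) = 0.171, d = 0.25 × 0.04 × 2.65 = 0.027, d/SE = 0.155, and the rejection rate is 1 − Φ(1.490) = 6.8%.

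A contrast of 1.4 is a reference point taken from the design. With F_A = 1 − (1 − F_S)^1.7 and an average of 55%, F_S = 46% and F_A = 64%, a ratio of 1.4. This is the ratio of liberation proportions. The ratio for the share of deaths after liberation remains an assumption.

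The last column is a simulation under the same assumptions (4,000 trials per row, observed minimum as worst value, 10 imputations, Rubin's rules).

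| m | s_S / s_A | d (SD) | SE | Rejects, formula | Rejects, simulated |
|---|---|---|---|---|---|
| 25% | 10% / 10% | 0 | 0.172 | 5% | 5% |
| 25% | 5% / 7% | 0.013 | 0.173 | 6% | 6% |
| 25% | 10% / 14% | 0.027 | 0.171 | 7% | 7% |
| 25% | 15% / 21% | 0.040 | 0.169 | 8% | 8% |
| 25% | 10% / 20% | 0.066 | 0.170 | 10% | 10% |
| 25% | 15% / 30% | 0.099 | 0.167 | 15% | 13% |
| 25% | 10% / 30% | 0.133 | 0.168 | 20% | 19% |
| 35% | 10% / 10% | 0 | 0.180 | 5% | 5% |
| 35% | 5% / 7% | 0.019 | 0.181 | 6% | 6% |
| 35% | 10% / 14% | 0.037 | 0.179 | 8% | 7% |
| 35% | 15% / 21% | 0.056 | 0.178 | 9% | 9% |
| 35% | 10% / 20% | 0.093 | 0.179 | 13% | 12% |
| 35% | 15% / 30% | 0.139 | 0.176 | 20% | 19% |
| 35% | 10% / 30% | 0.186 | 0.177 | 28% | 26% |

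In participants, 25% with 10% / 14% is about 3.4 against 4.8 per arm (136 × 0.25 × share).

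**The case against.** A reader might infer that anyone who dies after disconnection escapes the worst value. The text does not support that. Liberation needs 7 days without invasive ventilation, or earlier ICU or live hospital discharge. A participant reintubated within 7 days who dies in the ICU by day 28 already gets the worst value. Death in the ICU within 7 days without reintubation can be read either way, and the requirement that hospital discharge be live leans against calling it success. Since testing can start 24 hours after extubation, a clearly affected participant must go untested until the 7 days end or the ICU is left, and then die or enter palliative care. That may be uncommon.

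A reader might also infer that type I error control for CPF and MEP has been shown to fail. It has not. The larger rejection rates need two- to three-fold contrasts that nothing in the document supports. The direction is not fixed either: if sham had more untested deaths after liberation, the bias would go against active. Earlier extubation also opens the test window earlier, so more participants could be tested before death. The imputed value is a prediction from baseline factors, not a plain average, and frailty or SOFA may pull it down; the calculation ignores this.

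Finally, the full testing protocol (Appendix C) and the analysis plan are not shown. They may limit the test window or treat death before testing separately.

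All of this bears on frequency and size. The article still states the trigger for the worst-value rule, and that trigger gives the wrong result for deaths after liberation.

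**Conclusion.** The point holds in a limited form. As written, death or palliative care before testing leads to the worst value or to missing-at-random imputation according to whether successful liberation came first. The article has no separate rule for the second case and does not settle how an ICU death within 7 days of disconnection, without reintubation, is classed.

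The size cannot be found from the document. Under the stated assumptions the inflation is negligible with equal shares and modest (about 6% to 9% against 5%) at a 1.4-fold contrast. It reaches 10% to 26% only with two- to three-fold contrasts. The primary analysis is unaffected. The change should be made because both key secondary tests in the fixed sequence use the rule, and it is cheap to correct.

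**What to change.** Extend the worst-value rule rather than replace it:
- Keep the worst observed value for missing CPF or MEP in every participant with a competing event as now defined, including ICU transfer for a worsening condition. A rule naming only death and palliative care would move those transferred participants to missing-at-random imputation.
- Add any participant whose CPF or MEP is missing because of death or start of palliative care before the test, whether or not successful liberation had occurred. State that this includes death within 7 days of disconnection.
- Use missing-at-random imputation only for the remaining participants.

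This is a short change to the analysis plan, to be made before unblinding. It has two costs. A few more participants carry the worst value, so the SD rises slightly. Palliative-care status must also be available after liberation up to the test. The article lists mortality to hospital discharge and to 90 days, but uses palliative care only as an event before liberation, so its availability afterwards should be confirmed. With equal mortality and no cough effect the extended rule keeps the 5% level by construction, so that is not separate evidence for it.
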